#### Subgroup analyses

We will infer a subgroup effect if the interaction term of treatment and subgroup is statistically significant at *P* < 0.05.

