### Statistical considerations

#### Sample size

Sample-size calculation was based on a two-sided alpha error of 0.05 and a 80% power (beta). On the basis of respiratory insufficiency incidence after cardiac surgery, we anticipate that 25% of patients will have a PaO_2_/FiO_2_ ratio <200. We expect a reduction of 35% in the incidence of this parameter. We calculate that we will need a sample size of 263 patients per group, 789 in total. Including a dropout fraction of 10%, we calculate that we will need 870 patients to complete the trial.

A significant blind interim analysis (*P* < 0.0001) will be performed once half of the patients have been recruited to assess the recruiting progress and verify that the hypotheses assumed in the calculation of the sample size are correct.

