#### Data analysis

We will analyze patients in the treatment group to which they are allocated. Data will be analyzed with professional statistical software. Data will be analyzed according to the intention-to-treat principle and following a pre-established analysis plan. Dichotomous variables will be compared with the two-tailed *Χ*
^2^ test, using the Yates correction when appropriate. Continuous variables will be compared by analysis of variance or the nonparametric Kruskal-Wallis test, when appropriate. Relative risks with 95% confidence intervals, and differences between medians with 95% confidence intervals (using the Hodges-Lehmann estimation), will be calculated when appropriate. Two-sided significance tests will be used.

The major comparison will be between the two groups undergoing MV during CPB and the group with no MV.

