## Current trial status

Approval of the final protocol by the local committee at each center was obtained before starting recruitment. Patient recruitment at the coordinating center began in November 2014. As of 21 April 2017, 559 patients have been recruited into the CPBVENT trial. We plan to involve at least 20 of the most important Italian cardiac surgery centers. We expect to complete recruitment by June 2018 with results on the 1-year outcomes being available in 2019. The final results will be published as soon as the analysis has been completed.

In conclusion, after closing the present trial we hope to be able to recommend (or not) an easy and safe, evidence-based, lung-preservation strategy during CPB to all patients undergoing cardiac surgery.

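### The stated subgroup rule lets one unadjusted interaction at P<0.05 establish a subgroup effect, so the false-claim risk exceeds 5% once two or more subgroups are tested (minor)

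*Protocol article*

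**What the plan says.** The Subgroup analyses section of the protocol article is a single sentence: "We will infer a subgroup effect if the interaction term of treatment and subgroup is statistically significant", with the threshold set at P<0.05. It names no subgroups and gives no number of them.

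The neighbouring sections do not qualify the rule. Data analysis says "Two-sided significance tests will be used" and refers to analysis "following a pre-established analysis plan"; that plan is not shown. Sample size sets a two-sided alpha of 0.05 and 80% power for the main effect, on the basis that "we anticipate that 25% of patients will have a PaO_2_/FiO_2_ ratio <200" and "We expect a reduction of 35% in the incidence of this parameter". None of these sections adjusts for multiple interaction tests or describes the subgroup analyses as exploratory.

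Current trial status gives the use to which results will be put: "we hope to be able to recommend (or not) an easy and safe, evidence-based, lung-preservation strategy during CPB to all patients".

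**The concern.** The sentence does more than announce that interactions will be examined. It says what will be concluded from them: one result below 0.05 suffices to infer a subgroup effect. Each interaction has the full 5% to itself, so with two or more subgroups the overall chance of a false inference is above 5%.

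More than one factor is readily available. The eligibility table admits valvular, coronary, ascending aortic and combined surgery, and the data collection section lists Euroscore, ACEF and ARISCAT scores. At stake is the interpretation of the trial: a chance interaction could be reported as an established finding beside a recommendation meant for all patients.

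**Working it through.** **1. The plan's own sample size.** Inputs from the article: control incidence 25%; a 35% relative reduction, giving 0.25 × 0.65 = 16.25%; two-sided alpha 0.05; 80% power; 1:1:1 allocation; main comparison of the two ventilated groups with the unventilated group, hence 2:1. The normal-approximation formula for two proportions at 2:1 with continuity correction gives 263 in the control group, and 3 × 263 = 789. Both stated figures are reproduced. The trial is therefore sized for the pooled main effect, and 263 versus 526 are the right group sizes for step 3.

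**2. Chance of at least one false subgroup inference when the effect is uniform.** Let K be the number of interactions tested, each two-sided at 0.05. K is an assumption, because the article gives none.

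- Independent tests: 1 − 0.95^K. For example, K = 5 gives 1 − 0.95⁵ = 22.6%.
- Correlated tests: equicorrelated normal statistics with correlation ρ, by numerical integration of 1 − E{[Φ((1.96 − √ρ·X)/√(1−ρ)) − Φ((−1.96 − √ρ·X)/√(1−ρ))]^K}, with X standard normal.

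| K | ρ = 0.8 | ρ = 0.5 | Independent |
|---|---|---|---|
| 1 | 5.0% | 5.0% | 5.0% |
| 2 | 7.8% | 9.1% | 9.8% |
| 3 | 9.8% | 12.5% | 14.3% |
| 5 | 12.7% | 18.3% | 22.6% |
| 10 | 17.3% | 28.7% | 40.1% |

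With independent tests the figure is 48.7% at K = 13 and 51.2% at K = 14, so it first passes one half at 14. With a threshold of 0.05/K it stays at about 4.9% for K from 2 to 20.

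**3. Power for a real interaction.** Assumed scenario: two equal halves, control incidence 25% in both, relative risk 0.65 in one half and 1.0 in the other, 263 control and 526 ventilated patients in all. So each half has 131.5 control and 263 ventilated patients.

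- Difference in log odds ratios: ln(0.1625/0.8375) − ln(0.25/0.75) = −0.541.
- Variance in the half with an effect: 1/(131.5 × 0.25 × 0.75) + 1/(263 × 0.1625 × 0.8375) = 0.0406 + 0.0279 = 0.0685.
- Variance in the half without: 1/(131.5 × 0.25 × 0.75) + 1/(263 × 0.25 × 0.75) = 0.0406 + 0.0203 = 0.0608.
- Standard error: √(0.0685 + 0.0608) = 0.360, so the expected z is 0.541/0.360 = 1.50.
- Two-sided power at 0.05: about 32%. If the responding subgroup is 30% of patients instead of half, it is 27.6%.

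**4. What share of inferred effects would be false?** This needs an assumed proportion π of tested interactions that are real: (1 − π) × 0.05 / [(1 − π) × 0.05 + π × 0.325]. It gives 75% at π = 5%, 58% at 10%, 38% at 20% and 13% at 50%. The range is too wide, and too dependent on π, to carry the point.

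**The case against.** The strongest reply is that this is one sentence in a condensed article that refers to a separate analysis plan. The list of subgroups, any cap on their number, multiplicity handling and interpretive labels commonly sit in such a plan, so their absence here is no fault. That stands for the list and the cap: a reader might infer that the number of subgroups is unlimited, but the article's silence does not show that. Nor does the article show that an analysis plan could not mend the rule. A plan naming one subgroup gives exactly 5%, and one that adds an adjustment or an exploratory label deals with the problem. What the reply does not reach is the rule the article does state. Such a plan would have to depart from that sentence, so the two would need to be aligned.

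Second, requiring an interaction test rather than reading P values within subgroups is good practice, and leaving secondary interactions unadjusted is common. Both are true. The difficulty is the conclusion attached to the test, and formal adjustment can be optional if the exploratory label is there.

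Third, low power for interactions is usual in a trial sized on its main effect and is not an error; adjustment would lower it further. That also stands. The power figure is a reason for caution in interpreting a significant interaction, not a separate fault.

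Finally, nothing in the article ties the eventual recommendation to subgroup results, so an effect on that recommendation is possible but not documented.

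**Conclusion.** The point holds as a minor one about interpretation. As written, a single unadjusted interaction at P<0.05 is sufficient to infer a subgroup effect. If two or more subgroups are tested under that rule with nothing further, the chance of at least one false inference under a uniform effect exceeds 5%: about 8–10% for 2 subgroups, 13–23% for 5 and 17–40% for 10. These figures rest on an assumed number of subgroups and on correlations from 0.8 down to zero. The power of about 32% rests on the assumed interaction and equal halves.

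Two stronger readings are not supported. A reader might infer that a spurious subgroup claim is likely, but every scenario tabulated is below 50%, and the number of subgroups is not known. A reader might also infer that most claimed subgroup effects would be false, but that share runs from 75% to 13% as the assumed proportion of real interactions goes from 5% to 50%, and the documents give no basis for choosing. The primary analysis is unaffected.

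**What to change.** Replace the sentence under Subgroup analyses, and align the analysis plan with it, along these lines:

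> Subgroup analyses are exploratory. Interaction estimates with 95% confidence intervals will be reported for all pre-specified subgroups. An interaction at nominal P<0.05 will be treated as hypothesis-generating unless it remains significant after adjustment for the number of interactions tested (for example Holm).

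The exploratory label is the essential part; adjustment matters only if the investigators want to be able to claim a subgroup effect. The change needs no further patients or data. Its downside is that a nominally significant interaction can no longer be claimed as an established subgroup effect, and if adjustment is used, the already low power for a true interaction falls further.

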### Trial organization

The IRCCS San Raffaele Scientific Institute is the coordinating center for this study and is primarily responsible for the organization of the trial, development of the randomization scheme, study database, data consistency checks, data analysis and coordination of the study centers.

As the coordinating center we created an online platform (http://www.cpbvent.it) where investigators can electronically randomize the patient and load data in the online CRF. We also assist the other centers with administrative procedures as well as during the first cases.

All parts of the study will be conducted according to the Good Clinical Practice (GCP) Statement as well as Italian and international law on clinical research [39–41].

The trial structure includes the most important Italian adult cardiac surgical centers with experience of trials under GCP.

Safety monitoring activities performed by an independent monitoring body include reviewing the protocol with emphasis on data integrity as well as participant risk and safety issues, monitoring adverse events, and ensuring that practices are in place to safeguard the confidentiality of the data and results. The monitoring body must be separate and independent from the clinical staff or anyone responsible for patient care.

The monitoring body should not have scientific, financial or other conflicts of interest related to the trial. Current or past collaborators or associates of the principal investigator should not be a part of the monitoring body.

## Discussion

Postoperative pulmonary complications are frequent after cardiac surgery. Many factors may contribute to their development, in particular CPB. Most of these complications are not severe, but when a severe complication does occur, a patient’s life may be significantly threatened. Our effort in this trial is concentrated in particular on RF (see Table 2) which is still a major cause of mortality in cardiac surgery.

### Pathophysiology of CPB-related lung injury

A possible classification of CPB-mediated lung injury may follow the anatomical structures involved. Apostolakis et al. [42] reviewed the pathological alterations in the lungs after CPB. Such histological findings may contribute to hypoxemia, ventilation/perfusion ratio (V/Q) derangements and atelectasis. In fact, an important hypothesis regarding post-CPB lung dysfunction is related to an inflammatory reaction which has been linked to the use of the CPB circuit.

Many pathophysiological steps may be involved in lung injury. Pulmonary atelectasis is but one modifiable component of pulmonary dysfunction after CPB. Apnea during CPB has been suggested to promote the activation of lysosomal enzymes in the pulmonary circulation which in turn are correlated with the incidence of postoperative pulmonary dysfunction [43–46]. CPB duration has also been associated with lung injury and mortality. Ventilation-associated pneumonia (VAP) also showed a relation with CPB time and with preoperative pulmonary conditions [47, 48].

### Feasibility and safety of mechanical ventilation during CPB

Many clinical and preclinical trials have demonstrated the feasibility and safety of MV during CPB and introduced the key question of whether ventilating the patient’s lungs during CPB can have an impact on respiratory outcome. However, these are limited to the perioperative period and do not investigate enough clinically relevant endpoints. Nevertheless, these results showed the potential effectiveness of mechanical ventilation during CPB to prevent postoperative pulmonary complications (PPCs). Although it is currently unfeasible to recommend a unique strategy of lung preservation during CPB, the growing opinion is that keeping the lung ventilated, rather than interrupting ventilation during CPB, would improve respiratory outcome.

Schreiber et al. [11] analyzed different strategies to prevent CPB-related lung injury, finding an increase in oxygenation and a reduction in shunt fraction immediately after CPB when CPAP was applied during CPB. The application of low tidal/low frequency ventilation or vital capacity maneuvers during or after CPB was also helpful in order to prevent lung injury. Nevertheless, they found a rather limited impact on postoperative clinical outcomes. However, we find these results with surrogate endpoints [11], encouraging the investigation of the real clinical impact of ventilation during CPB.

In order to minimize potential biases, we decided to keep a rigorous scheme of mechanical ventilation for the patients included in our study. In particular, ventilation with higher tidal volumes has been associated with worse respiratory outcome in cardiac surgery [27–29].

Before planning our trial, we reviewed all the randomized clinical trials on ventilation during CPB in elective adult cardiac surgery, published from 2000 to the present year [11, 49–63]. All randomized trials take into consideration small-sized samples and limited setting.

### Limitations

The CPBVENT trial will enroll patients undergoing elective cardiac surgery with CPB. Eligible patients usually have a preserved cardiac function and no significant risk factors for postoperative respiratory insufficiency [26, 27]. Our intention is to eliminate the possible selection biases and build a more homogeneous sample. This could be a limitation, since the inclusion of higher-risk patients might be the basis of a higher-powered trial, but we believe that a “clean” experimental setting would make it easier to eliminate confounding factors and the final results will be more extendible to the majority of our patients. Furthermore, eligible patients will be all cardiac surgery patients undergoing median sternotomy and CPB, including patients undergoing mammary artery bypass graft surgery. We are aware that this could be a limitation, because ventilation during mammary artery isolation may make surgery more difficult.

Other possible limitations of our trial could be the constant PEEP level and short duration of recruitment maneuvers used. A longer recruitment maneuver could significantly impair hemodynamic stability because of the increase in intrathoracic pressure in a delicate phase of surgery such as weaning from CPB.

We also acknowledge that the primary endpoint ratio that we chose is very wide and could include many different conditions. A possible alternative endpoint would have been the incidence of PPCs in the study population. On the other hand, some false positives might occur if we consider PPCs after cardiac surgery. For instance, pneumothorax is much more frequent than in other surgical settings since all patients undergo central venous catheterization and the surgery involved might include incision of the pleural surfaces. Moreover, pleural effusion and pulmonary edema might also be consequences of depressed cardiac function, with well-functioning lungs. Moreover, we will collect all data about lung complications after surgery and provide detailed etiologies for gas exchange problems in our final results.

Furthermore, we acknowledge that the incidence of 25% for a PaO_2_/FiO_2_ ratio <200 is high and, even if it is the one we experienced in our daily practice, the risk of a final underpowered result is still present. Our choice was driven by our clinical experience but also by feasibility. On the other hand, this study is still the largest ever performed on this topic and we hope to provide some important insights into CPB-related lung injury pathophysiology and prevention.

Pulmonary artery perfusion during CPB [63] and pulsatile pulmonary perfusion [64] have been proposed as a further approach to attenuate the CPB-related lung dysfunction. Still, the currently available techniques of pulmonary perfusion during CPB are still emerging and their feasibility is strongly linked to the surgeon’s experience.

Finally, we are aware that the results obtained from a specific subgroup of patients, with strict inclusion criteria, may not be generalizable to the whole population. However, since this is the first large trial ever performed on this topic, we decided to create a clean experimental setting. Further research will be necessary to assess whether our findings are extendible to other subgroups and to the general population of patients undergoing to cardiac surgery with CPB.

## Current trial status

Approval of the final protocol by the local committee at each center was obtained before starting recruitment. Patient recruitment at the coordinating center began in November 2014. As of 21 April 2017, 559 patients have been recruited into the CPBVENT trial. We plan to involve at least 20 of the most important Italian cardiac surgery centers. We expect to complete recruitment by June 2018 with results on the 1-year outcomes being available in 2019. The final results will be published as soon as the analysis has been completed.

In conclusion, after closing the present trial we hope to be able to recommend (or not) an easy and safe, evidence-based, lung-preservation strategy during CPB to all patients undergoing cardiac surgery.
